### Statistical consideration

#### Sample size

Twelve sites (four hospitals, eight hospices) will be involved in the feasibility study, and these will be randomised to either standard intervention A or standard intervention B. There will be a separate randomisation process for the hospitals and the hospices. The target is to recruit 200 participants from the 12 sites within a period of one year; the end of the trial will occur when either 200 participants have been recruited, or the trial has been ongoing for one year (and inadequate numbers of participants have been recruited).

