#### Analysis

A ’case‘ of hyperactive delirium is considered to be a participant that scores +2 to +4 on the mRASS [28], and is treated by the clinical team with an appropriate anti-psychotic or sedative drug to treat hyperactive delirium (terminal agitation). Participants who do not fall into this category will be considered as ’non-case‘. This dichotomous outcome will be used as the primary endpoint for the analysis.

The analysis evaluating the difference in proportions of participants experiencing hyperactive delirium between the two interventions will be a logistic regression with the occurrence of hyperactive delirium as the dependent variable and interventions (A or B), cluster and cluster type (hospital or hospice) as explanatory variables. The analysis will be based on the intention-to-treat (ITT) population, and will furnish estimates of the proportion of subjects suffering from hyperactive delirium for each intervention together with an estimate of the coefficient of variation of true proportions between clusters within each intervention arm. The latter of these estimates is an important requirement for determining the sample size aspect of a future cluster randomised study designed with adequate power to evaluate the impact of the intervention including CAH. It is judged that recruitment of 200 participants in 12 clusters in the feasibility study will provide a realistic estimate.

The logistic regression analysis will allow the testing of the hypothesis of no difference in the proportion of hyperactive delirium experienced between groups treated by either intervention. The intervention including CAH will be considered an improvement on the other intervention, in this and any future definitive study, only if the proportion of hyperactive delirium sufferers is reduced by at least 20 %.

It is considered unlikely that this statistical analysis of the feasibility study will be able to test this hypothesis with sufficient power, but its results, together with information gained from other aspects of the study management, will be used to design a definitive study.

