From a statistical perspective, the estimates of the proportion of subjects suffering hyperactive delirium for each intervention, and the coefficient of variation of true proportions between clusters within each intervention, obtained from the feasibility study, will be used to determine the number of clusters and sample size necessary to detect a difference of 20 % in the proportion of hyperactive delirium sufferers between the interventions with 80 % power using a two-sided 5 % significance level. This calculation will form part of the design of the definitive study.

Should the number of clusters and sample size in the feasibility study retrospectively be found to provide the necessary power to test the hypothesis, the statistician will provide this information to the study team as input into their decision as to whether a definitive study is required.

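### Power computed after the fact from this study's own estimates is to inform whether a definitive trial is needed; an interval set against the 20% threshold would serve better

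*Protocol article*

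**What the plan says.** The Sample size section gives no power calculation, which is reasonable for a feasibility study: "The target is to recruit 200 participants from the 12 sites within a period of one year". The Analysis section says of its hypothesis test that "It is considered unlikely that this statistical analysis of the feasibility study will be able to test this hypothesis with sufficient power". It then explains that the event proportions and the CV of true proportions between clusters, both estimated here, will give the number of clusters and participants "necessary to detect a difference of 20 % in the proportion of hyperactive delirium sufferers between the interventions". The design standard for that calculation is "80 % power using a two-sided 5 % significance level".

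The section closes with the clause at issue: "Should the number of clusters and sample size in the feasibility study retrospectively be found to provide the necessary power to test the hypothesis". If so, this is passed to the team "as input into their decision as to whether a definitive study is required". Nothing in the section ties that decision to the estimated difference and its confidence interval. The same section counts hydration as an improvement "only if the proportion of hyperactive delirium sufferers is reduced by at least 20" per cent, without saying whether this is absolute or relative.

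**The concern.** Power is a design quantity. Once the data are in, how far the study has answered its question is shown by the estimated difference and its interval, compared with the smallest difference that matters. Recomputed power adds nothing to that, and here its main uncertain input is a between-cluster CV from a handful of sites. When the CV happens to be underestimated, the recomputed power is too high. The clause also acts in one direction only, because the team is told when power is found sufficient. It therefore tends to pick out studies in which the CV came out low by chance. At stake is whether a study designed for feasibility is treated as having been large enough to make a definitive trial unnecessary.

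**Working it through.** The article states no power figure for this study, so there is none to reproduce.

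**Inputs from the article.** 200 participants and 12 sites (Sample size); a 20% target, 80% power and two-sided 5% (Analysis).

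**Assumptions.** Six sites per arm; m = 17 per site (200/12 = 16.7; the results barely change); CV k from 0 to 0.40; control rates of 35, 40 and 50%. The article gives no control rate for its endpoint. The Background gives 25 to 85% for delirium in general.

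**Step 1: power for a fixed target.** The usual coefficient-of-variation formula for cluster trials gives

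power = Φ( |p0 − p1| × √[(c − 1)/V] − 1.96 ), with V = p0(1 − p0)/m + p1(1 − p1)/m + k²(p0² + p1²) and c = 6.

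For 35% against 15% (20 percentage points), the binomial part of V is 0.2275/17 + 0.1275/17 = 0.0209, and p0² + p1² = 0.145.

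- k = 0: V = 0.0209, power 87%
- k = 0.15: V = 0.0241, power 82%
- k = 0.25: V = 0.0299, power 73%
- k = 0.40: V = 0.0441, power 57%

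So if k is estimated as zero and the control rate as 35%, the formula returns 87% whatever the true k is.

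For a relative 20% (35% against 28%) at k = 0.25, V = 0.0378 and power is 12%. For control rates of 25 to 50% and k of 0.15 to 0.40, the relative reading gives power of about 8 to 21%.

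**Step 2: how well six sites estimate k.** In beta-binomial simulation with true k = 0.25, the one-arm moment estimate runs from 0 to about 0.50–0.57 (2.5th to 97.5th percentile). It is exactly zero in about 19% of studies at a control rate of 50%, 27 to 29% at 40%, and 32% at 35%.

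**Step 3: the retrospective figure.** For each simulated study I re-estimated the control rate and k, recomputed power for the 20-point target, and counted results of at least 80%. The ranges cover different ways of combining the arms' CV estimates.

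| Control rate | True k | True power | Studies reported at ≥ 80% |
|---|---|---|---|
| 35% | 0.15 | 82% | 48–62% |
| 35% | 0.25 | 73% | 36–49% |
| 35% | 0.40 | 57% | 19–29% |
| 40% | 0.25 | 65% | 19–31% |
| 50% | 0.15 | 67% | 4–8% |
| 50% | 0.25 | 53% | 2–5% |
| 50% | 0.40 | 35% | 1–2% |

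At a control rate of 40% and k = 0.25, the retrospective figure spans about 30 to 90% from study to study, against a true 65%. In the first row power really is adequate, yet the check misses this in roughly 40 to 50% of studies. Under the relative reading at control rates of 35 to 50%, it essentially never reached 80%.

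**Step 4: if the observed difference were used instead.** Power would then be Φ(|z| − 1.96), a function of the p-value alone: 50% at p = 0.05, and 80% only when z = 1.96 + 0.84 = 2.80, that is p = 0.005. Power for the fixed target does not behave this way. Its rank correlation with the p-value was only about +0.09 to −0.42.

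**The case against.** Several stronger readings are tempting, and the article does not support them.

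- *Recomputed power decides whether the definitive trial goes ahead.* The clause calls it "input into their decision as to whether a definitive study is required", with no rule attached. The Analysis section adds information from other aspects of study management, and a process evaluation runs in parallel.
- *The calculation merely restates the p-value.* The text sets the target at 20% in advance and nowhere says that the observed difference will be used. Both arms' estimated proportions are named as inputs, so some doubt remains, but Step 4 applies only under that less natural reading.
- *A non-significant result will be read as showing that hydration does not work, or a chance-large one as definitive.* The article says neither, and its authors expect too little power.

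The size of the problem also depends heavily on unstated inputs. At a control rate of 50%, or with a relative target at control rates of 35 to 50%, the clause is close to inert. At a control rate of 25% with a 20-point target, the formula gives 82 to 97% for k up to 0.40, so a finding of adequate power would be correct.

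These limits stand. What they leave untouched is that the check rests on a poorly estimated CV, and that the interval answers the team's question directly.

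**Conclusion.** The point holds in a limited form. The article plans a retrospective power check, built on this study's own proportions and CV, as one input to whether a definitive trial is required. With a 20-percentage-point target and a control rate of 35%, a study with true power of about 57 to 73% would be called adequately powered in very roughly a fifth to a half of cases. With a control rate of 50%, or a relative target at control rates of 35 to 50%, the check would almost never be triggered. It is thus misleading in some plausible settings and inert in others. Even where power truly is adequate, it says less than the interval does. Because the 20% is not defined as absolute or relative, the trigger itself is undefined.

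The control rates, the CV range, the 6:6 split and equal site sizes are assumptions; the percentages show the order of magnitude and are not predictions. The conduct of the study is unaffected. The wording should be changed before the data are analysed.

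**What to change.** Delete the retrospective-power paragraph at the end of the Analysis section and replace it with wording such as:

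*The estimated difference in the proportion of participants with hyperactive delirium will be reported with a 95% confidence interval that allows for clustering by site, and compared with the 20% threshold [state: percentage points or relative reduction]. Together with the feasibility and process-evaluation findings, this will inform the decision on a definitive study. The event proportions and between-cluster coefficient of variation, with their uncertainty, will be used only to determine the size of that study.*

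The planned hypothesis test and the 20% improvement criterion can stay, provided the 20% is defined in the same way throughout.

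The cost is one paragraph and no new data. The sponsor gives up the option of declaring this study adequately powered after the fact.

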### Governance

#### Safety reporting

All adverse events (AEs) and serious adverse events (SAEs) will be documented in the CRF, and reviewed by the Chief Investigator and Trial Monitoring Committee (TMC). As the study is being undertaken in patients in the last days of life, the progression of existing problems and the development of routine end-oflife problems (for example, hyperactive delirium/’terminal agitation‘, excess respiratory secretions/’death rattle‘) are not considered to be SAEs.

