In 2013, Parry et al. conducted a rapid evidence review of the literature on pathways focussed on the dying phase in end-of-life care and their key components, and concluded that “the current research evidence base is not sufficient to inform specific recommendations to use or not to use clinically-assisted nutrition and/or hydration” [6]. The review included the new randomised controlled trial [16], which again did not address the specific issue of the routine use of CAH at the end of life. Thus, Bruera et al. only included patients with evidence of dehydration, and patients were given relatively low doses of fluid (1 L per day), and the fluids were continued for a variable duration, that is, “until the patient was unresponsive, developed progressive coma, or died”. The conclusion of this study was that “hydration at 1 L per day did not improve symptoms, quality of life, or survival”.

The purported positive effects of CAH include the maintenance of patient comfort (for example, prevention of thirst, prevention of dry mouth), and the maintenance of renal perfusion/prevention of accumulation of toxins and drugs (prevention of delirium, prevention of opioid toxicity) [17]. In contrast, the purported negative effects of CAH include problems due to fluid overload (for example, worsening of peripheral oedema, worsening of cardiac failure), and problems due to fluid-related complications (for example, worsening of vomiting, worsening of respiratory secretions) [17]. In addition, it has been claimed that ketones and other by-products of dehydration can have positive effects on the patients’ condition/symptom control (analgesic effects, sedative effects). As intimated above, there is little evidence to support/refute these effects in the general population.

Patients with cancer may develop a range of problems in the last days of life, including delirium (’terminal agitation’/’terminal restlessness’ [18]), excess respiratory secretions (’death rattle’), urinary retention or urinary incontinence, and continuance or exacerbation of other symptoms (for example, pain, dyspnoea, nausea and vomiting) [19].

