### Study procedures

During the treatment period patients will be reviewed at least every four hours, and an assessment made as to whether or not certain symptoms are present, that is, hyperactive delirium (‘terminal agitation‘), pain, excess respiratory secretions (‘death rattle‘), nausea and vomiting, dyspnoea and urinary continence. Agitation will be given a score (see below), but the other symptoms will simply be recorded as present or absent. In addition, changes in regular medications, use of as required (PRN) medications, oral intake, urinary continence, and (if appropriate) parenteral fluids administered, adverse events relating to parenteral fluids and requirements for re-cannulation will also be noted. Data will be obtained from the participant’s observation chart and the participant’s drug chart(s); these documents are considered source documents in this study.

At the end of the study the researcher will record the participant’s outcome, including the date of death/withdrawal, and the reason for withdrawal (if appropriate). The end of study occurs when an individual participant either: a) survives for ≥ 14 days; b) dies (expected outcome); or c) is withdrawn from the study Table 2.

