#### Trial Monitoring Committee

The study will have a Trial Monitoring Committee (TMC), which will consist of an independent Chairperson (Consultant in Palliative Medicine), the Chief Investigator, the Clinical Trial Unit Lead, the Lead Research Nurse, the Statisticians, the Ethical Advisor, patient/carer representatives and one of the Principal Investigators. The TMC will meet approximately once a quarter (until the end-of-study report has been completed). The TMC will review all aspects of the study, particularly any safety issues.

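### The SAE exemption has no exception for events suspected to be caused by the study fluid, although the protocol lists some of the exempt events as purported harms of that fluid

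*Protocol article*

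**What the plan says.** Safety reporting (under Governance) begins with a general duty: "All adverse events (AEs) and serious adverse events (SAEs) will be documented in the CRF", with review by the Chief Investigator and the TMC. It then exempts "the progression of existing problems and the development of routine end-oflife problems" from SAE status. The examples are hyperactive delirium and respiratory secretions, and the sentence closes with "excess respiratory secretions/’death rattle‘) are not considered to be SAEs". The only reason given is that participants are in the last days of life.

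The Background lists the purported negative effects of CAH in two groups. The first is overload, worded as "problems due to fluid overload (for example, worsening of peripheral oedema, worsening of cardiac failure". The second group covers complications of giving fluid, and its examples are "worsening of vomiting, worsening of respiratory secretions".

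Other safety provisions are spread over the article:
- Study procedures has secretions, pain, dyspnoea, and nausea and vomiting charted at least four-hourly as present or absent. Where fluids are given, "adverse events relating to parenteral fluids and requirements for re-cannulation will also be noted".
- Table 2 has a daily row for adverse events, separate from the four-hourly symptom row.
- Outcome measures makes fluid-related problems and changes in CAH status secondary endpoints.
- The Trial Monitoring Committee section says "The TMC will review all aspects of the study, particularly any safety issues", with meetings about once a quarter.

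**The concern.** An exemption for expected events makes sense in a dying population, because nearly every participant would otherwise generate SAE reports for the natural course of disease. That reasoning covers background events. It does not cover the same kind of event when the clinical team suspects that the study fluid caused or worsened it, and the text does not separate the two.

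At stake is how serious harm in arm B is labelled and counted. A site that follows the rule literally could classify a serious, suspected fluid-related episode of respiratory secretions as not an SAE. A low count of fluid-related SAEs at the end of the trial would then partly reflect the definition. That matters because this is a feasibility study meant to inform a definitive trial. The article also calls the 1 L per day of the earlier randomised studies relatively low, while Table 1 goes up to 2 L/24 h.

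**Working it through.** The document states no figure on this point and no arithmetic applies. The check sets the purported harms in the Background against the exemption in Safety reporting.

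| Purported fluid harm (Background) | Covered by the SAE exemption? |
|---|---|
| Worsening of respiratory secretions | Yes, directly: excess secretions are a named example of a non-SAE |
| Worsening of vomiting | Yes where vomiting pre-exists, as progression of an existing problem; the Background also counts exacerbation of nausea and vomiting among last-days problems |
| Worsening of peripheral oedema | Yes where oedema pre-exists, as progression of an existing problem |
| Worsening of cardiac failure | Largely not in play: cardiac failure is the example of an excluded contra-indication under Inclusion/exclusion criteria |
| New-onset fluid overload | Not plainly: it is not progression of an existing problem, and oedema and cardiac failure are not in the Background's list of last-days problems |

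**Step 1. Is there an overlap?** Yes. It is direct for secretions. For vomiting and oedema it runs through the Background's worsening examples and needs the problem to be present already.

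**Step 2. Is the exemption qualified anywhere?** Study procedures, Table 2, Outcome measures, Inclusion/exclusion criteria and the Trial Monitoring Committee section were read for a condition by arm, severity or relatedness. None contains one.

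**Step 3. What survives the exemption?** The adverse event record, the fluid-related adverse event record, the change in CAH status, and review by the Chief Investigator and TMC all survive. Secretions are charted in both arms, so their frequency can still be compared between arms.

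**Step 4. What does not survive?** The SAE classification. The symptom chart cannot stand in for it, because apart from agitation it records only presence or absence and so does not separate a mild episode from a serious one. The fluid-related adverse event record does carry relatedness, but the article does not link it to seriousness or to the exemption.

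**The case against.** The strongest reply is that nothing is hidden. Safety reporting itself requires all adverse events to be documented and reviewed, fluid-related events are noted separately, and fluid problems are secondary endpoints. A participant whose fluid was changed because of secretions would appear in these records. This stands. A reader might infer from the exemption that serious fluid toxicity goes unrecorded or is kept from the TMC, and the document does not support that.

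A second reply is that the overlap is narrower than it first looks. This also stands. The Background does not name progression of existing problems, in those words, as a fluid harm. Known cardiac failure should not be in the trial, and new-onset overload is not clearly exempt. Reading the rule as exempting all fluid toxicity would go too far.

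A third reply is that this is a condensed article, that the full protocol (version 5) is not shown, and that seriousness definitions and relatedness assessment are often left to it. An exemption for expected events is also a reasoned choice in a comparison of standard interventions outside the medicinal-product regulations. This stands in part. The full protocol may hold an exception, and then the remedy is simply to state it. But the article states the exemption outright and unconditionally, so the point rests on what the text fixes and not on a missing detail.

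Finally, the symmetrical four-hourly chart is better evidence of an excess in arm B than relatedness judgements made by staff who know the arm. That is correct for the comparison between arms. It does not answer the question of how an individual serious case is classified.

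**Conclusion.** The point holds in a limited form. As written, a serious event suspected to be caused by the study fluid can be classed as not an SAE. This follows directly for respiratory secretions, and for vomiting and peripheral oedema where they were already present. The loss is one of classification, not of data or of review.

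No number can be attached. The documents give no rate of serious secretions, vomiting or oedema in either arm, and any assumed excess would only restate the assumption. The conclusion rests on reading the exemption as it stands in the article and on no exception existing in the full protocol. The primary analysis is unaffected. The change is worth making because it is cheap and bears on participant safety, in a trial where many participants are expected to be unable to consent for themselves.

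**What to change.** Reconcile the Background, Study procedures and Safety reporting by adding one sentence to Safety reporting: an event that would otherwise be exempt is reported as an SAE when it meets a seriousness criterion and is suspected to have been caused or worsened by parenteral fluid. Leave the exemption unchanged for all other events. If the full protocol already says this, repeat it here.

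A change in CAH status should not be a trigger on its own. Changing or stopping a fluid is not in itself a seriousness criterion, and using it alone would turn non-serious events into SAEs.

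The cost is one sentence in the protocol, a matching line in the site safety instructions, and a few extra SAE forms. Those forms would come from arm B only and rest on unblinded judgements of relatedness. They serve safety oversight and should not be used to compare the arms. The change touches no fluid volume, treatment or stopping decision.
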